**Table 5b. Prostate cancer specific mortality, stratified by subgroups**

---

*GLEASON SCORE: 6*

Active monitoring protocol

Surgery

Radiotherapy protocol

*GLEASON SCORE: 7+*

Active monitoring protocol

Surgery

Radiotherapy protocol

*CLINICAL STAGE: T1c*

Active monitoring protocol

Surgery

Radiotherapy protocol

*CLINICAL STAGE: T2*

Active monitoring protocol

Surgery

Radiotherapy protocol

---

1. Definitely or probably due to prostate cancer or its treatment, as established by the Independent Cause of Death Evaluation Committee. 2. Likelihood ratio interaction test of the null hypothesis, no difference in relative effectiveness of the three treatments between levels of a subgroup

## 9. APPENDIX

The following standard assessment tools have been completed by men participating in the ProtecT study:

- Expanded Prostate Index Composite
- International Consultation on Incontinence Questionnaire (ICIQ)
- International Continence Society urinary function (ICSmaleSF)
- International Continence Society sexual function (ICSsex)
- EORTC QLQ-C30 cancer-specific impacts
- Hospital Anxiety and Depression Scale
- Short Form 12 (SF-12) mental and physical subscales
- EuroQoL-5D (EQ-5D) generic quality of life

This is the final published version of the article (version of record). It first appeared online via Centre for Open Science at [dx.doi.org/10.17605/OSF.IO/JCT49](https://doi.org/10.17605/OSF.IO/JCT49). Please refer to any applicable terms of use of the publisher.

## University of Bristol - Explore Bristol Research

### General rights

This document is made available in accordance with publisher policies. Please cite only the published version using the reference above. Full terms of use are available:  
<http://www.bristol.ac.uk/red/research-policy/pure/user-guides/ebr-terms/>

## 1. INTRODUCTION & PURPOSE

*This document details the statistical analysis proposed and the presentation that will be followed, as closely as possible, when analysing and reporting the median **15-year** results from the **Prostate Testing for Cancer and Treatment ( ProtecT ) Study**. As far as possible this plan will follow the approaches in the main ProtecT statistical analysis plan written for the primary analysis of median 10-year follow-up, which is available at: <https://njl-admin.nihr.ac.uk/document/download/2021093>*

The purpose of the plan is to:

1. Make explicit the details of the planned analysis, as agreed with the Trial Steering Committee.
2. Ensure that the analysis is appropriate for the aims of the trial, reflects good statistical practice, and that interpretation of *a priori* and post-hoc analyses is appropriate.
3. Explain in detail how the data will be handled and analysed to enable others to perform the actual analysis in the event of sickness or other absence, or to replicate the analyses

Additional exploratory or auxiliary analyses of data not specified in the protocol are permitted but fall outside the scope of this analysis plan (although such analyses would be expected to follow Good Statistical Practice).

The analysis strategy will be made available if required by journal editors or referees when the main papers are submitted for publication. Additional analyses suggested by reviewers or editors will, if considered appropriate, be performed in accordance with the Analysis Plan, but if reported the source of such a post-hoc analysis will be declared.

Amendments to the statistical analysis plan will be described and justified in the final report of the trial.

## **2. SYNOPSIS OF STUDY DESIGN AND PROCEDURES**

**IMPORTANT:** *This synopsis is purely to provide background information for those reading the statistical analysis plan. It does not replace the study protocol; the current version of which must be consulted for all other purposes.*

### **2.1. Trial objectives and aims**

The ProtecT trial was designed in the late 1990s and early 2000s to compare the major conventional treatments for patients with clinically localised prostate cancer detected through population-based PSA testing. The three treatments were radical prostatectomy, external beam three-dimensional (3D) conformal radiotherapy, and active monitoring.

#### **2.1.1. Primary objective**

In men with localised prostate cancer detected through population-based PSA testing, to compare definite or probable prostate cancer specific mortality (including definite or probable intervention related mortality) at a median of 10 years following random allocation to radical prostatectomy, external beam three dimensional (3D) conformal radiotherapy, and active monitoring.

#### **2.1.2. Secondary objectives**

To make the same comparison on a number of secondary outcome measures, including overall survival, clinical disease progression, treatment complications, lower urinary tract symptoms, quality of life, and sexual function. To estimate the resource use and costs of case-finding, treatment and follow-up, and to compare costs and outcomes of treatment in terms of survival and health related quality of life.

### **2.2. Trial design and configuration**

A three parallel groups randomised controlled trial.

### **2.3. Trial centres**

Recruitment to the trial took place at general practices in and around nine study centres across the UK: Newcastle, Sheffield, Bristol, Cardiff, Edinburgh, Birmingham, Leicester, Cambridge, and Leeds.

## 2.4. Eligibility criteria

### 2.4.1. Inclusion criteria

- Men
- Age 50-69 years on the date of preparation at the general practice of the list of potential participants
- Able to give written informed consent to participate
- Fit for any of the three treatments and with a life expectancy of at least 10 years
- Registration with the participating general practice on the date of the PCC
- For randomisation: clinically localized prostate cancer (confirmed by isotope bone scan in men with PSA of 10ng/L or more) diagnosed by 10-core biopsy following a PSA level of 3ng/L or more.

### 2.4.2. Exclusion criteria

- Concomitant or past malignancies (other than a small treated skin cancer)
- Prior treatment for prostate malignancy
- Serious cardiac or respiratory problems in the previous 12 months of the PCC, e.g. stroke, MI, heart failure, COPD
- Kidney dialyses or transplantation
- Bilateral hip replacement
- Previous entry to the ProtecT study at a prior general practice
- PSA 20ng/L or more at diagnosis

## 2.5. Description of interventions

The **Active Monitoring Protocol** aimed to avoid immediate radical treatment whilst assessing the disease over time, with a review and the opportunity for radical treatment if there was evidence of disease progression. PSA levels were measured and reviewed every three months in the first year and twice yearly thereafter. Changes in PSA levels were assessed, and a rise of at least 50% over the previous 12 months triggered repeat testing within six to nine weeks. If the PSA levels were persistently raised, or the patient had other concerns, a review appointment was made to consider treatment options.

The **Radiotherapy Protocol** began with neoadjuvant androgen suppression, given for three to six months before and concomitantly with 3D-conformal radiation therapy delivered at 74 Gy in 37 fractions.

**Surgery** was a radical retropubic prostatectomy procedure. The surgical approach was left to the discretion of the surgeon, and was most commonly open, but laparoscopic, or robot-assisted approaches were permitted from 2003.

## 2.6. Randomisation procedures

Randomisation was stratified by centre with stochastic minimization by age at invitation, Gleason score (primary and secondary grades), and mean of baseline and first biopsy PSA results. Men who declined randomisation were offered identical follow-up and formed an observational patient preference cohort.

## 2.7. Blinding

The process used to assess cause of death was adapted from the PLCO algorithm and ERSPC process. The medical records of deceased participants were summarised by trained researchers, anonymised and reviewed by an independent endpoint committee. Table 1 presents the classification of deaths by study arm.

## 2.8. Trial committees

*For the current period of follow-up, ProtecT has a Trial Steering Committee, chaired by [name] (Imperial College).*

## 2.9. Outcome measures

### 2.9.1. Primary outcome

The primary outcome is definite or probable prostate cancer mortality, including intervention-related deaths, at a median 10 years' follow-up.

*We will repeat the analysis of definite or probable prostate cancer mortality, including intervention-related deaths, at 10 years (with all participating men having more than 10 years' follow-up) and at the median 15 years' follow-up.*

*As previously the plan is for the primary outcome measure to be determined by the independent cause of death committee. If this proves not possible, we will rely on certified underlying cause of death where necessary.*

### 2.9.2. Secondary outcomes

*Secondary clinical and patient-reported outcomes to be presented in the 15-year results papers are:*

- *overall mortality*

- *metastatic disease*
- *clinical disease progression*
- *initiation of long-term hormone therapy*
- *patient reported outcomes (PROMs)*

*Metastatic disease is defined as positive imaging showing bony, visceral and/or lymph node metastases, or PSA above 100; or bone marrow infiltration with associated systemic symptoms.*

*Clinical disease progression will be measured as person-years free of the consequences of disease progression. Signs of disease progression will include evidence of metastatic disease; the initiation of long-term hormone therapy; diagnosis of clinical T3 or T4 disease; or ureteric obstruction, rectal fistula, or the need for a permanent catheter when these are not considered to be a complication of treatment. There will be a review of cases where disease progression or metastatic disease are uncertain.*

As the ascertainment of clinical disease progression may differ between the three study arms, we will also present the initiation of long-term hormone therapy, to indicate those men whose disease is no longer curable.

The reporting of metastatic disease, clinical disease progression, and initiation of long-term hormone therapy is conditional on securing the data.

*The patient-reported outcomes which have been measured are listed in the Appendix. These measures are derived from validated questionnaires and have been completed at recruitment, at first biopsy, six months after randomisation, and yearly thereafter. These measures will be reported in a separate companion paper, to be submitted for publication at the same time as the primary outcomes paper.*

## **2.10. Interim analysis**

*There have been no analyses of the outcome data that have accumulated since publication of the findings at median ten-years follow-up.*

### **3. GENERAL ANALYSIS CONSIDERATIONS**

#### **3.1. Analysis populations**

The primary analysis data set is all men **randomly allocated** to one of the three management options being compared in the ProtecT trial.

#### **3.2. Procedures for missing data**

Where a man has omitted responding to a small number of items on a patient reported outcome measure, these will be imputed as per the guidance for that measure.

Where the patient has not responded to any or most of the items on a measure, the main analysis of patient-reported outcomes will NOT be based on data with those missing scale scores imputed. However, the amount of missing data, by allocation arm, will be presented. All men providing at least one post-randomisation patient-reported measure will be included in the relevant analysis.

#### **3.3 Definitions of treatment received**

Men were considered to have received each of the treatments according to the following definitions; men who did not fulfil these were excluded.

1. Active Monitoring (AM) if there were  $\geq$  two PSA tests and no radical treatment in the 12 months following diagnosis.
2. Surgery (RP) if RP carried out within 12 months following diagnosis.
3. Radiotherapy (RT) if treatment protocol was started within 12 and completed within 15 months.

## 4. DESCRIPTION OF PARTICIPANT CHARACTERISTICS

### 4.1. Disposition

Details of the recruitment of the ProtecT randomised trial cohort, up to the point of randomisation, were presented in the *Baseline Paper* (Lane et al, 2014). Details of how many men were excluded and for what reasons are presented. The subsequent flow of patients through the trial will be summarised in a CONSORT diagram that will include the numbers randomised to the three treatment groups, losses to follow-up and the numbers analysed. *This extends the diagram in [name] et al (2016) to make clear losses to follow-up since the median ten-year follow-up (Figure 1).*

## 5. ANALYSIS OF EFFECTIVENESS

### 5.1. Summary of outcomes to report at median 15 years follow-up

The following summaries of the outcome events will be presented for each treatment allocation group:

- Number of deaths due to prostate cancer.
- Prostate cancer mortality at 15 years, with 95% confidence interval.
- Prostate cancer mortality per 1,000 person years of follow-up, with 95% confidence interval.
- Kaplan-Meier survival of death from prostate cancer as a function over time.

The following summaries will be presented for the clinical secondary outcome events:

- Number of events.
- Events per 1000 person years of follow-up, with 95% confidence interval.
- Kaplan-Meier overall survival and survival free of disease progression as functions over time

In addition, if the data can be obtained, the Kaplan-Meier cumulative incidence of the uptake of radical treatment will be presented for the three treatment groups as a function over time.

### 5.2. Prostate cancer mortality at median 15 years follow-up

*This analysis will be conducted on an intention-to-treat basis comparing allocated groups. Deaths occurring until a median of 15-year follow-up has accumulated (23:59 on Monday 23rd November 2020) will be included in the locked database. We will allow up to 30th June 2021 to be notified of deaths (we may revise this deadline for notification if the COVID-19 outbreak causes delays).*

Prostate cancer (definite, probable, or intervention-related) mortality will be compared between the three treatment groups using Cox's proportional hazards regression adjusted for study centre (all nine centres distinguished using dummy variables), age at baseline (continuous measure in years), Gleason score (2-6, 7, 8-10), and PSA at baseline (continuous measure in ng/ml, log-transformed to accommodate positive skewed distribution):

$$h(t) = h_0(t) \exp\{\beta_{1j}x_{1i} + \beta_{2k}x_{2i} + \beta_3x_{3i} + \beta_{4m}x_{4i} + \beta_5 \ln.x_{5i}\}$$

$\beta_{1j}$  is the log hazard ratio comparing two of the treatment arms, with two of the three pairwise comparisons being available from a single iteration of the analysis (i.e.  $j=1,2$  the estimated comparisons depending on the choice of comparator treatment).  $x_{1i}$  is the treatment allocation (0,1,2) for participant  $i$ .  $\beta_{2k}$  ( $k=1$  to 8) captures differences in the hazard of the primary outcome event between study centres,  $x_{2i}$  being the study centre for participant  $i$ .  $\beta_3$  is the linear effect of age, with  $x_{3i}$  being the age in years for participant  $i$ .  $\beta_{4m}$  ( $m=1,2$ ) accommodates the effect of Gleason score category with  $x_{4i}$  being the Gleason score category for participant  $i$ . Finally  $\beta_5$  is the linear effect of log-transformed PSA level,  $x_{5i}$  being the PSA level at diagnosis for participant  $i$ .

Plots and tests based upon Schoenfeld residuals will be investigated to determine whether the proportional hazards assumption is reasonable; if not the model will be elaborated to allow for a changing magnitude of treatment effect with time.

The hazard ratio and 95% confidence interval for the treatment effect estimated in each pairwise comparison of allocated treatments will be presented, but pairwise significance tests will only be conducted if a test of an equal 15-year disease specific mortality risk across all three arms yields a p-value of less than 0.05 (Table 3). This conditional approach keeps the overall false positive rate at 5% and has been found to maintain power in simulation studies (Bauer 1991).

The competing risk of all-cause death is not anticipated to influence the estimation of the treatment effect on the risk of prostate cancer mortality. Age is the only strongly influential risk factor shared by all-cause and prostate cancer mortality, and age is included as a covariate in all models.

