#### *Updated background (2022)*

Currently, based on the median 10-year findings from ProtecT, men, clinicians and policy-makers know that a man diagnosed with clinically localised prostate cancer will have a very low risk of dying from prostate cancer (~1%) whether they have radical treatment or active monitoring, but an increased risk of developing metastases with active monitoring compared with surgery or radiotherapy. What we do not know is whether or when this additional rate of developing metastases in active monitoring will be translated into an increased risk of dying of prostate cancer earlier than if they had surgery or radiotherapy, or whether the even higher risk of dying from other causes including cardiovascular disease and other cancers will intervene.

In addition, there were some small (but not significant) differences between surgery and radiotherapy at 10 years in terms of primary treatment failure and biochemical progression which may or may not translate into significant differences in metastases or progression. If this occurs by the median 15-year follow up, this would also change policy and practice. If these small differences favouring surgery turn into significant differences in the analyses with more years of follow-up, then the higher levels of sexual dysfunction and urinary incontinence could form a better trade-off. In active monitoring, there is a gain immediately from avoiding a loss of sex life and retaining continence, without knowing whether the higher risk of metastases will result in a

shortening of life expectancy and the impact of the development of metastases and their treatment on quality of life.

The median 15 year analyses will provide patients, clinicians, and policy makers with more information y about the 'trade-off' between oncological outcomes for disease progression and side-effects of treatments in the short- and medium-term, longer follow-up to a median of 20 years is essential to provide definitive information about mortality and disease progression.

**Original text:** 4. TRIAL DESIGN (Figure 1)

*Original trial figure (Fig 1a)*

[figure not shown]

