### **The Number of Participants**

The original sample size calculation was presented in published protocol. The ProtecT study randomly allocated 545 men to active monitoring, 553 men to surgery, and 545 men to radiotherapy. Amongst these men, at median 10-year follow-up, there were 8, 5 and 4 prostate cancer deaths respectively. There were very few withdrawals at the time of the median 10-year analyses in randomised men. A simple extrapolation from the occurrence of prostate cancer deaths during the median 10-year follow-up, suggests that by the end of 2020 the number will have doubled from 17 to 34 among those randomised. If there is an increase in the incidence rate of prostate cancer death, as may result from the number of metastatic disease cases that have been diagnosed, then conditional power of 67%, 78%, and 85%, would result from the occurrence of 48, 60, and 72 prostate cancer deaths respectively.

A formal sample size calculation was not undertaken for men in other groups (advanced cancer, comorbidities or with and initial PSA of 20ng/ml or above). All men in these groups will be followed up observationally.

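### Whether the mortality effect changes after 10 years is left to a proportional hazards check with little power at the projected deaths; a hazard ratio beyond 10 years should be reported in any case

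*Supplement*

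**What the plan says.** The 15-year SAP, section 5.2, compares the arms with an adjusted Cox model that holds one log hazard ratio per treatment contrast over all follow-up. On proportional hazards it names plots plus "tests based upon Schoenfeld residuals will be investigated to determine whether the proportional hazards assumption is reasonable; if not the model will be elaborated", so that the effect may vary over time. It gives no significance level, time scale, cut-point or form for the elaborated model. No period-specific hazard ratio is planned otherwise.

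The protocol (version 5.5), section 3.2, Updated background (2022), names as unknown "whether or when this additional rate of developing metastases in active monitoring will be translated into an increased risk of dying" from the disease sooner than after radical treatment. Appendix 2, The Number of Participants, records that the trial "randomly allocated 545 men to active monitoring, 553 men to surgery, and 545 men to radiotherapy" and that, at the median 10-year analysis, "there were 8, 5 and 4 prostate cancer deaths respectively". By simple extrapolation it expects that "by the end of 2020 the number will have doubled from 17 to 34 among those randomised", with 48, 60 and 72 deaths as scenarios if the death rate rises.

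Several outputs are planned whatever the check shows:
- Kaplan-Meier curves by arm (SAP 5.1 and Figure 3);
- prostate cancer mortality by arm at 10 and 15 years with intervals (SAP Table 1);
- a repeat of the 10-year analysis now that every man has passed 10 years (SAP 2.9.1);
- a cumulative incidence approach (protocol Appendix 2).

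For patient-reported outcomes, SAP 5.3 tests the newly observed period, 73 to 144 months, on its own. Appendix 2 says the 20-year analyses will use similar approaches to the 15-year ones.

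**The concern.** If excess metastases under active monitoring become deaths only later, the treatment effect is non-proportional by construction. The plan nevertheless makes a constant effect the default and departs from it only when a diagnostic objects. With few deaths, a diagnostic that does not object is weak evidence of a constant effect. The reported hazard ratio would then mix an early and a late effect in proportions set by when deaths happened to occur, and nothing would estimate the late contrast with its uncertainty. The mortality outcome would have no period-specific analysis, although the patient-reported outcomes do.

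**Working it through.** **Inputs.** Arms 545, 553 and 545; early deaths 8, 5 and 4; total deaths 34, 48, 60 or 72 (all protocol Appendix 2). Assumed, because the documents do not say: a switch at about 10 years, a check at two-sided 5%, and the 17 known deaths as the early period. They were counted at a calendar census at median 10 years, so this last split is approximate.

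**The plan's own figures.** 2 x (8 + 5 + 4) = 34, as stated. Conditional powers of 67, 78 and 85% are given for 48, 60 and 72 deaths, for an effect that is not stated. Schoenfeld's formula for monitoring against both radical arms with a constant hazard ratio of about 0.475 gives 68, 78 and 85%, so they are plausible. No power is given for the proportional hazards check.

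**Power of the check, known switch point.** Take one radical arm against monitoring, with hazard ratio 1 for the first 17 deaths and 0.5 in both radical arms for the remaining L. The variance of a log hazard ratio is about 1/d1 + 1/d2.
- Early: 17/3 = 5.67 deaths per arm; variance 2/5.67 = 0.353.
- Late, L = 17: 8.5 and 4.25 deaths; variance 0.353. z = ln 2 / sqrt(0.706) = 0.825; power about 13%, miss 86.9%.
- Late, L = 55: 27.5 and 13.75 deaths; variance 0.109. z = ln 2 / sqrt(0.462) = 1.02; power about 17.5%, miss 82.5%.
- At 48 and 60 deaths the same steps give 84.5% and 83.3%.
- With unlimited late deaths, z = ln 2 / sqrt(0.353) = 1.17 and the miss rate is still about 78%. The early period is the limit.
- With a 10% test, the miss rate is 78.7% at 34 deaths and 73.0% at 72.

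**Power of the check, as usually run.** Schoenfeld-type score tests were simulated with rank, identity and log time (1,500 trials per setting; follow-up 11 to 20 years, about 20% other-cause deaths by 15 years, no covariates).

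| Contrast | Miss rate, 34 deaths | Miss rate, 72 deaths |
|---|---|---|
| Pairwise | 89-90% | 85-88% |
| Three-arm, 2 df | 89-91% | 86-89% |
| Monitoring v both radical arms | 88-91% | 84-87% |

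Near 65 deaths, one setting of the last contrast fell to 83%; simulation error is about sqrt(0.84 x 0.16 / 1500) = 1 percentage point. A separate 20,000-run simulation of the three-arm test on ranked event times detected the switch 11, 12 and 12% of the time at 34, 48 and 72 deaths.

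**What the single hazard ratio would be.** Radical arms (1,098 men) against monitoring (545), as a crude ratio of deaths per man. The observed early ratio is (9/1098)/(8/545) = 0.56. With late hazard ratio 0.5, monitoring takes 545/(545 + 0.5 x 1098) = 49.8% of late deaths; with late hazard ratio 1 it takes 545/1643 = 33.2%.

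| Early deaths | Late HR | 34 deaths | 48 deaths | 72 deaths |
|---|---|---|---|---|
| Expected under early HR 1 | 0.5 | 0.70 | 0.63 | 0.59 |
| Observed 8/5/4 | 0.5 | 0.53 | 0.52 | 0.51 |
| Observed 8/5/4 | 1 | 0.74 | 0.81 | 0.87 |

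Example, second row at 34 deaths: monitoring 8 + 8.47 = 16.47, radical 9 + 8.53 = 17.53; (17.53/1098)/(16.47/545) = 0.53. At 34 deaths the first and third rows (0.70 and 0.74) are opposite answers to the late-effect question, yet give nearly the same single figure.

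**The case against.** Four points deserve weight.

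- The trigger is plots as well as tests, with no stated rule, so a miss rate computed for a 5% test is not the miss rate of the plan. This stands. The result must be read as a range under assumptions, though the plots rest on the same few deaths.
- The known early deaths already favour radical treatment, at 0.56. If the late effect is 0.5, they hardly dilute it. This stands, although 17 deaths are too few to exclude a true early hazard ratio of 1.
- The time course is shown anyway, by the curves, the 10- and 15-year risks and the repeated 10-year analysis. This stands in part. The repeat covers the early period, but the 15-year results all accumulate from randomisation, and none is a contrast beyond 10 years with an interval.
- A late-period estimate will be imprecise. For a true late value of 0.5, the pairwise 95% interval would run from about 0.16 to 1.60 with 17 late deaths, 0.21 to 1.18 with 31 and 0.26 to 0.96 with 55. If the early value is truly 1, pairwise power is 21% for the late period alone against 13% for the blended hazard ratio at 34 deaths, and 56% against 45% at 72. The number of deaths is the main limit. A wide interval still states what is known about the late effect; a diagnostic that fails to object does not.

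**Conclusion.** The point holds as a modest, inexpensive improvement. At 34 to 72 deaths, a 5% Schoenfeld-type test would miss a change from 1 to 0.5 at about 10 years roughly 84 to 91% of the time. Its silence is therefore close to uninformative on the extension's own question. The result rests on the assumed switch time and test level and on treating the 17 census deaths as the early period. Recruitment ran from 2001 to 2009 and the census was in November 2015, so follow-up then ranged from about 6 to 14 years.

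Three stronger readings are not supported:
- A reader might infer that a late effect would be averaged away. The size and direction of the blending depend on the early effect. With the observed early deaths, a late 0.5 is reported almost intact, while a late null would look like a benefit of 0.74 to 0.87.
- A reader might infer that the question goes unanswered. The planned curves and risks describe the time course; what is missing is the late contrast and its interval.
- A reader might infer that the 5% false positive rate is broken. If the overall test became a joint 4-df test whenever the check fired at 5%, the rate would be about 0.95 x 0.05 + 0.05 x exp(-1.7485) x 2.7485 = 7.1%. Nothing prescribes that. SAP 5.2 asks for a test of equal 15-year risk, and footnote 1 to Table 1 describes an adjusted likelihood ratio test across the three arms.

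**What to change.** In SAP 5.2, replace the conditional sentence with a fixed rule. Whatever the Schoenfeld output shows, report the pairwise hazard ratios with 95% intervals for 0-10 years and beyond 10 years from randomisation, beside the overall hazard ratio. Present them as estimates without extra significance tests, and keep the Schoenfeld plots and tests as description only. State the number of deaths in each period by arm. Write the same rule into the 20-year analysis plan. If the 15-year analysis has already been run, label the split there as an added analysis.

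As a clarification only, state that the overall test opening the pairwise tests remains the adjusted 2-df likelihood ratio test of the Table 1 footnote, whichever model is later shown. Section 5.2 currently points to a Table 3, but the 15-year SAP contains only Tables 1 and 2.

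The cost is a few sentences and one Cox fit with follow-up split at 10 years, on data already held. The late-period intervals will be wide, and the 10-year cut is a fixed choice, although it matches the trial's own earlier analysis horizon.
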